**Figure 1 jmft70052-fig-0001:**
[figure not shown]
Schedule of enrollment, intervention conditions, and assessments. *After completing the third assessment, each condition will have the opportunity to receive the materials from the other condition. Implementation outcomes (e.g., eligibility, enrollment, and completion rates) will be collected on a continuous basis from enrollment to T3.

### Participants

2.2

Eligible parents must (a) live in South Carolina, (b) be able to speak English or Spanish, (c) have access to a device to be able to attend Zoom video calls, and (d) must not have received any parent training services or health services aimed at improving their children's behaviors or lifestyle habits, such as sleep or physical activity promotion programs, in the 12 months before enrolling in the study. Parents must also be the primary caregivers of a child that (e) is between 3 and 6 years of age, (f) is Black/African American or Latiné/Hispanic, and (g) their child must not have any psychological or chronic health issues that significantly interfere with their communication (e.g., child does not understand basic instructions from their parent) or that limit their ability to engage in physical activity (e.g., child uses a wheelchair). Primary caregiver refers to a parent who resides in the same household as the child for at least 50% of the time and has primary custody of the child. We chose to include children with physical or mental health diagnoses as long as these issues did not interfere with key intervention targets, such as their ability to benefit from parenting strategies and adjust their lifestyle behaviors (e.g., physical activity level). These criteria were selected because they align with our universal prevention approach that targets families across the risk spectrum. Target recruitment for this study is 60 families (*n* = 30 experimental, *n* = 30 control).

### Recruitment and Randomization

2.3

Participants will be recruited using a multifaceted strategy. This involves distributing flyers via email to community partners and displaying them at various locations like schools, daycares, churches, grocery stores, and health clinics. We will also participate in community events, such as back‐to‐school gatherings. To further assist with recruitment, we will hire three designated recruiters who are well‐connected in the community and have experience as community health workers. These recruiters will also act as interventionists (also referred to as parent coaches) for our study. Interested parents can express their interest by calling our designated study phone number, sending an email, or completing an online eligibility form by scanning the QR code shown on the study flyer. After that, research assistants from the ROOTS team will confirm their eligibility during a screening call. Informed consent will be gathered through this screening call and by reviewing qualtrics online forms. Black and Latiné participants will be randomized separately to ensure adequate representation of each ethnic‐racial group within each treatment condition (participants of AfroLatiné descent will be randomized based on language preference). To create each randomization scheme, we will use Excel's random number generator function to produce and save 30 random numbers. These assignments will be hidden in Excel to prevent access by research staff making screening calls. After consenting to participate and completing the T1 assessment, participants will receive a study ID number. This ID number will be added to the appropriate randomization scheme (either Black or Latiné) in the order of enrollment. The random assignment will then be revealed by a designated study staff member.

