### Study Setting and Design

2.1

Because the protocol will be implemented virtually, families living anywhere in the state of South Carolina will be able to participate. To pilot the feasibility of the ROOTS program, the study will use a longitudinal two‐arm randomized control trial design in which families are randomized into a parenting intervention (*n* = 30) or a control (*n* = 30) condition on a 1:1 ratio. We selected a nutrition control condition that is a similar length (6 weeks) and provides a similar structure (offers parents new strategies and a workbook to reflect on their progress and goals). This decision was based on empirical evidence suggesting a need for alternative approaches to intervention research to maximize participant engagement and minimize ethical concerns related to withholding services from underserved populations (Henry et al. 2017). Assessments will occur at three timepoints: pre‐intervention (T1), post‐intervention (T2), and 3‐month follow‐up (T3). After completing the third assessment, each condition will have the opportunity to receive the materials from the other condition.

The hybrid effectiveness‐implementation approach adopted for this study examines intervention outcomes while concurrently assessing barriers and facilitators related to successful program delivery (see Figure 1). Blinding will occur at several levels, primarily with participants, outcome assessors, and data analysts. For example, intervention participants will not be aware of which intervention group is considered the treatment or control; rather, they will be instructed that the study seeks to compare the effects of two health interventions. Outcome assessment will be conducted using Qualtrics, which prevents potential bias from using unblinded assessors. Blinding will also occur at the data analyst level, specifically related to assessing outcomes.

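### Two separate lists of 30 Excel random numbers, with no stated restriction, group quota or overflow rule, do not ensure the planned 30:30 split or the intended representation of each group in each arm

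*Protocol article*

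**What the plan says.** Section 2.1 (Study Setting and Design) plans 30 ROOTS families and a "control (*n* = 30) condition on a 1:1 ratio". Section 2.2 (Participants) repeats the arm sizes: "Target recruitment for this study is 60 families".

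Section 2.3 (Recruitment and Randomization) gives both the purpose and the mechanism. The purpose: "Black and Latiné participants will be randomized separately to ensure adequate representation of each ethnic‐racial group within each treatment condition". AfroLatiné families go to a list by language: "participants of AfroLatiné descent will be randomized based on language preference". The mechanism, for each scheme, is Excel's "random number generator function to produce and save 30 random numbers". Study IDs then enter the Black or the Latiné list in order of enrolment, after consent and the T1 assessment.

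The article does not say how a number becomes an arm. It names no block, sort or fixed 15:15 count, no quota per group, and no step for a full list. The recruitment criterion in section 2.5.1 is open-ended: 60 or more families counts as a go, and 40–50 as amend.

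Section 2.8 names child age, gender and socioeconomic factors as model covariates. Race/ethnicity and preferred language appear in section 2.5.4 among factors to be examined as potential covariates or moderators. Section 2.8 also compares effect sizes by delivery language and by ethnic-racial background.

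**The concern.** Stratified randomisation balances strata only if allocation within each stratum is restricted, for example by blocks. Separate lists of independent draws behave exactly like one simple randomisation, so keeping two lists does not by itself achieve what section 2.3 says they are for.

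The fixed list length is a second problem. Two lists of 30 make exactly 60 slots, but nothing stated makes enrolment split 30/30 by group. Once one group passes 30, the next family has no prepared assignment, and someone must improvise.

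Three things are at stake: chance imbalance between arms on ethnic-racial group, and with it language; thin cells in the planned subgroup comparisons; and ad hoc allocation at the point where a list is exhausted.

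**Working it through.** **Inputs.** 60 families, 30 per arm, 1:1 (sections 2.1 and 2.2). Two strata with 30 numbers each, used in order of enrolment (section 2.3). The share of Black and Latiné families is not given; I assume 50% to 70% in the larger group.

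**The plan's own figure.** 2 × 30 = 60 slots, which agrees with the target of 60. Whether 30:30 follows depends on how the numbers become arms, so I take both readings.

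**Reading A: each number sets an arm independently (50:50), both lists full.**
- 15:15 in one list: C(30,15)/2^30 = 0.144. In both lists: 0.144² = 0.021.
- 30:30 overall: C(60,30)/2^60 = 0.103.
- 18:12 or worse in a given stratum: 2·P(X ≥ 18), X ~ Bin(30, 0.5), = 0.362. In at least one of the two: 1 − (1 − 0.362)² = 0.59.
- 20:10 or worse: 0.099 in a given stratum and 1 − (1 − 0.099)² = 0.19 in at least one.
- 36:24 or worse overall: 2·P(X ≥ 36), X ~ Bin(60, 0.5), = 0.155.
- Share of Black families differing between arms by 20 percentage points or more (enumerating both strata): 0.155.
- Efficiency relative to equal arms, 4·n1·n2/N²: 4·36·24/3600 = 0.96 overall at 36:24, and 4·20·10/900 = 0.89 within a stratum at 20:10.

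**Reading B: the numbers sort 15 + 15 labels.** A full list gives 15:15, and two full lists give 30:30. Each list is then a single block of 30, so a part-filled list is hypergeometric:

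| Slots used | P(arm difference ≥ 4) | P(arm difference ≥ 6) | Reading A, P(≥ 4) |
|---|---|---|---|
| 24 | 0.17 | 0.017 | 0.54 |
| 20 | 0.25 | 0.050 | 0.50 |

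**List exhaustion, under either reading.** Let X ~ Bin(n, s) be the number in the larger group, with no quota (assumption). A list runs out if X > 30 or n − X > 30. At n = 60 this is 1 − P(X = 30).

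| Larger-group share s | P(a list runs out), n = 60 | Expected families without a slot, n = 60 | P(a list runs out), n = 50 |
|---|---|---|---|
| 50% | 0.90 | 3 | 0.12 |
| 60% | 0.97 | 6 | 0.45 |
| 70% | above 0.99 | 12 | 0.92 |

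**With small blocks.** Permuted blocks of 2 and 4 cap the arm difference in each stratum at 2 at any time, whatever the group mix.

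**The case against.** The strongest reply is that a lack of restriction is not stated. Random numbers in a spreadsheet are often used to sort a prepared list, and two sorted 15:15 lists would fit the planned 30:30 exactly. An article also condenses a fuller protocol, which may hold the number-to-arm rule, a quota of 30 per group and an overflow step. This stands in part. A reader might infer that the lists are unblocked and that the design balances neither arms nor strata; the article neither says that nor rules it out, and the Reading A figures are conditional. The point survives because the article does describe a generator, a list length, an order of use and a purpose, and on neither reading does that description secure the purpose.

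Other limits also stand:
- A reader might infer that the lists fail unless exactly 30 of each group enrol. That is true only at 60 enrolled. A list fails when a group exceeds 30; 25 + 25 exhausts neither, and a part-filled list still gives valid assignments.
- Exact 15:15 is never promised, and adequate representation is a weaker aim. Even under independent draws, about 90% of strata would be closer than 20:10.
- Imbalance might be called confounding of the effect sizes. Chance imbalance under valid randomisation is not bias, and confidence intervals allow for it.
- Coach mix might seem to be at risk through ethnic-racial matching. It is not: matched coaches lead ROOTS sessions (section 2.4.3), while the control is self-directed (section 2.4.5).
- Small blocks make allocation somewhat more guessable, and the recruiters are also the coaches. Assignment after consent and T1 limits this.

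**Conclusion.** The concern holds in a limited form. As described, the method does not ensure 30:30 or the stated representation of each group in each arm. Under independent draws, separate lists add nothing over simple randomisation: 0.10 for 30:30, 0.59 for 18:12 or worse in at least one stratum, 0.10 for 20:10 or worse in a given stratum. Under sorted 15:15 lists, balance is exact only when the lists fill.

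The list-length weakness does not depend on that choice. With 60 enrolled, it has probability 0.90 to above 0.99 over the assumed range of group shares. This rests on there being no quota and no later extension of a list; the article mentions neither.

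The consequences are modest. The estimates stay unbiased and efficiency is still 0.96 at 36:24. What remains is avoidable chance imbalance on ethnic-racial group and language, which the named model covariates do not address, and improvised allocation if a list is exhausted.

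**What to change.** 1. For any allocations still to be made, generate each stratum's list with permuted blocks of randomly varying size (for example 2 and 4), longer than 30 so that accrual may differ by group. State how a number becomes an arm. Cost: minutes of work, and slightly more predictable allocation, limited by varying the block size and revealing the arm only after T1.
2. In all cases, include the randomisation stratum (Black or Latiné list, with AfroLatiné families coded by the list actually used) as a fixed covariate in the Aim 2 mixed models. Cost: one parameter per model.
3. Recruitment began in May 2024 and follow-up is due to end in fall 2025, so allocation may already be complete. If so, replace the statement that separate randomisation secures representation with the method actually used, the achieved arm sizes by stratum, and what was done if a list ran out. Cost: a sentence and a small table.

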### Intervention Development and Delivery

2.4

#### Program Development

2.4.1

To develop the ROOTS program, we utilized intervention mapping (Fernandez et al. 2019), a structured, theory‐ and evidence‐based approach for designing culturally responsive health promotion interventions. This process involved multiple steps, such as identifying target health outcomes (i.e., child emotional and physical health problems), determining malleable influences (e.g., parenting practices, ethnic‐racial socialization, and child health behaviors), selecting and integrating strategies, and planning for implementation and evaluation. For example, to gather information about child health and identify culturally relevant determinants, we conducted qualitative interviews with 47 community members, including Black and Latiné parents and community health workers (Cooper et al. 2024). Participants emphasized the need to integrate ethnic‐racial socialization, healthy lifestyle practices, and positive parenting into one coherent intervention. This community input directly shaped the content and delivery format of the ROOTS program.

#### Program Content

2.4.2

ROOTS draws primarily from the Triple P—positive parenting program (Sanders 2012), an internationally disseminated intervention supported by over 200 randomized controlled trials and available in 24 languages (Sanders 2023). The ROOTS program integrates Triple P strategies with culturally grounded ethnic‐racial socialization content from one talk at a time (stein 2021; Soltero et al. 2021) and health promotion recommendations for young children (Allen et al. 2016; Brown et al. 2016; Jones et al. 2021; see Table 1). The six‐session curriculum teaches caregivers to use positive parenting techniques to support racial pride, prepare children for bias, and encourage healthy routines around sleep, screen use, and physical activity. The one talk at a time intervention was chosen for its feasibility with Black and Latiné families and for its compatibility with strategies taught in Triple P. While there are various cultural differences between non‐Latiné Black and Latiné families, there is evidence that these positive parenting and ethnic‐racial socialization strategies can be tailored to fit the needs of both groups. For example, strategies for promoting racial pride, such as celebrating cultural holidays, telling family stories, and reading books about culture, can apply to members of various racial or cultural groups, even though the cultural content within these strategies may differ (e.g., celebrating Juneteenth vs. Dia de los Muertos).

**Table 1 jmft70052-tbl-0001:** Session‐by‐session outline.

[figure not shown]

*Note:* Color‐coded emboldened text specifies the type of added content, such that red represents ethnic‐racial socialization content, blue represents sleep content, black represents screen use content, and gold represents physical activity content.

Abbreviations: Activity, physical activity; ERS, ethnic‐racial socialization; SU, screen use. [Color figure can be viewed at wileyonlinelibrary.com]

The ROOTS program's incorporation of healthy lifestyle behaviors is addressed mainly in Session 1, during which parents are educated on how sleep, screen time, and physical activity issues can contribute to child behavior problems. Parents learn about the current recommendations for promoting healthy child sleep habits (Allen et al. 2016), physical activity and sedentary behavior (Brown et al. 2016), and managing screen use (Jones et al. 2021). In later sessions, parents are taught positive parenting strategies that can be used to improve these lifestyle behaviors. For example, parents may be guided to use praise and behavioral reinforcement charts to encourage healthy sleep habits and to respond to bedtime misbehavior with consistent consequences such as planned ignoring or time out.

#### Program Format and Delivery

2.4.3

ROOTS consists of 6 weekly one‐on‐one sessions, each lasting approximately 60–90 min. Sessions follow a structured format that includes a review of homework activities, didactic teaching, interactive discussions, and role play. Parents meet virtually via Zoom in either English or Spanish, depending on their preference. Sessions are led by trained interventionists who match the racial and ethnic backgrounds of participants. Parents receive a ROOTS toolkit by mail, which includes a workbook, culturally relevant children's books to support ethnic‐racial socialization, a program schedule, and study‐branded materials (e.g., handheld fan, hand sanitizer). Participants also receive weekly text message reminders about homework and appointment dates.

#### Program Interventionists

2.4.4

Interventionists will be community‐integrated professionals (e.g., school counselors, community health workers) selected based on their shared cultural backgrounds with participants and prior experience working with families. These interventionists will also serve as designated recruiters for the study (described above). All interventionists will complete formal Triple P training (i.e., Standard Level 4 4‐day virtual training) and additional ROOTS‐specific training. This training will include: (a) reviewing the ROOTS facilitator manual, (b) viewing video demonstrations of each session led by the PI with a practice family, (c) participating in live role‐plays and supervision, (d) completing post‐session fidelity checklists where they self‐rate their coverage of topics, and (e) receiving ongoing consultation with the PI, consistent with the Triple P training model (Sanders et al. 2020).

#### Nutrition Control Condition

2.4.5

Parents in the active control condition will receive a six‐session self‐directed nutrition intervention based on best practices for healthy eating. These materials were compiled from Myplate.gov and Nibbles for Health and cover a range of topics, including nutrition basics, trying new foods, breakfast and snacks, fruits and vegetables, protein and dairy, and bread and grains. Parents are given a workbook that includes empty spaces for goal setting and behavior tracking, as well as a study overview schedule and study swag. After the 3‐month follow‐up assessment (T3), parents in the nutrition control condition will receive the parenting intervention materials and have the option to attend a 1‐h consultation session to provide an overview of the materials.

### Measures

2.5

#### Feasibility and Implementation Outcomes

2.5.1

Two prominent implementation science frameworks will be used to guide the evaluation of feasibility and implementation outcomes: (a) the reach, effectiveness, adoption, implementation, maintenance (RE‐AIM; Glasgow et al. 1999) model to assess key implementation outcomes and (b) the consolidated framework for implementation research 2.0 (CFIR; Damschroder et al. 2022) to assess various determinants shown to impact intervention delivery. The RE‐AIM model is a prominent framework for assessing the relevance of interventions in practice settings and provides several important implementation outcomes to consider, such as evaluating whether the intervention was delivered as intended and measures related to feasibility, acceptability, adaptation, and fidelity. We will assess feasibility (or reach as defined in the RE‐AIM framework) using the following benchmarks (progression criteria) in accordance with the traffic light approach (Mellor et al. 2023): *feasibility of recruiting* (go/proceed with RCT: recruit ≥ 60 families in 12 months, amend/proceed with changes: recruit 40–50 families in 12 months, stop/do not proceed unless changes are possible: recruit ≤ 30 families in 12 months), *feasibility of enrollment* (go: ≥ 70% of eligible families enroll, amend: 40%–50%, stop: ≤ 30%), *feasibility of session completion* (go: ≥ 60% of randomized participants complete all six sessions, amend: 40%–50%, stop: ≤ 30%), and *feasibility of assessment completion* (go: ≥ 60% complete all three assessments, amend: 40%–50%, stop: ≤ 30%). These progression criteria were based on past family‐based intervention studies with minoritized samples (Smokowski et al. 2018; Weeland et al. 2025) and are intended to be interpreted as guidelines rather than strict rules. We recognize that some outcomes may fall between categories (e.g., 60% enrollment falls below the “go” threshold of 70% but above the “amend” threshold of 50%). In such cases, we will apply a structured consensus process involving multiple team members (e.g., PI, research staff, community partners) who review the full pattern of feasibility data across domains (e.g., enrollment, attendance, fidelity, and satisfaction). Decisions will be made based on the overall weight of evidence rather than any single metric (Mellor et al. 2023). For example, if enrollment falls into the “amend” range but other domains indicate strong feasibility (e.g., high session and assessment completion), the team may decide to proceed with minor adjustments rather than redesign the protocol. Conversely, consistent “amend” scores across domains may warrant amendments before proceeding. This approach allows for flexibility while ensuring that decisions remain transparent, data‐driven, and collaboratively reviewed.

Additionally, the CFIR framework provides 67 constructs presumed to impact intervention delivery, such as the characteristics of the intervention (or innovation), the delivery setting, and the recipient population, which have been shown to be particularly important considerations when working with underserved populations (Brownson et al. 2021). These CFIR constructs are assumed to be determinants of the implementation outcomes specified by the RE‐AIM model, helping to understand the conditions needed to support successful intervention delivery. Understanding which CFIR constructs influence adoption, implementation, and maintenance can inform the development of targeted strategies that balance scientific rigor with real‐world relevance. CFIR helps explain *why* implementation succeeds or fails, while RE‐AIM captures the practical outcomes of intervention delivery, such as the *who*, *what*, *where*, *how*, and *when* (King et al. 2020). Used together, these frameworks can strengthen implementation planning, improve fidelity and uptake, and support the long‐term sustainability of an intervention. In our study, we will use a combination of qualitative and quantitative measures to assess these various implementation outcomes (specified by RE‐AIM), as well as assess the intervention conditions that influence intervention success (specified by CFIR; see Table 2; King et al. 2020; Konrad et al. 2022).

**Table 2 jmft70052-tbl-0002:** Implementation outcome table organized by RE‐AIM and CFIR domains.

Domain	Definition	Qual	Quant	Description of measures
RE‐AIM framework (implementation outcomes: who, what, where, how, when?)				
**R**each	Number, percentage, and representativeness of participants reached, including characteristics of nonparticipants		●	Record of recruitment, enrollment, and retention rates (for assessments and intervention) in accordance with our progression criteria
**E**ffectiveness	Impact of the intervention on outcomes of interest	●	●	*Quantitative*: T1, T2, and T3 measures of parent and child health outcomes (see Table 3)*Qualitative*: parent interviews assessing intervention satisfaction and perceived benefits
**A**doption	Number, percentage, and representativeness of settings and staff willing to adopt the intervention	●	●	*Quantitative*: interventionists’ satisfaction with the intervention (e.g., acceptability of intervention measure)*Qualitative*: in our formative work, we surveyed community health workers about the feasibility of ROOTS. We also plan to interview interventionists about their satisfaction with ROOTS and desire to implement it after the project ends
**I**mplementation	Degree to which the intervention is implemented as intended, including staff adherence to protocols, consistency of delivery, and associated time and cost	●	●	*Quantitative*: assessments of various aspects of fidelity (post‐session checklist, process quality measure)*Qualitative*: assess interventionists and participants on perceived barriers and facilitators for implementation
**M**aintenance	Degree to which the intervention is integrated into an organization's standard practices and long‐term operations	●	●	*Quantitative and qualitative*: assessments of interventionists’ willingness to continue implementing ROOTS and perceived ease of implementation (e.g., Feasibility of Implementation Measure)
CFIR framework (implementation conditions, barriers, facilitators)				
Innovation characteristics	Whether intervention demonstrates advantages over current practices and can be adapted for successful implementation in the target context	●		Qualitative interviews with parents and interventionists about perceived intervention barriers and facilitators, such as number and length of sessions, virtual format, ease of delivery
Outer setting	Whether implementing the intervention is important at this time, addresses a critical gap in care, and aligns with current priorities in the larger context (e.g., state)	●		Formative work involved assessing current community needs and delivery feasibility, including perspectives on parenting support, child health, and intervention characteristics and format (Cooper et al. 2024)
Inner setting	Whether implementing this intervention is feasible for a given setting (e.g., school, organization)	●		Formative work involved assessing community needs and delivery feasibility within various contexts. We will also interview interventionists about feasibility of ROOTS' virtual, community health worker delivery format.
Characteristics of individuals	Whether parents and providers view the intervention as valuable and relevant to families	●	●	Participants' and interventionists' perceptions of the acceptability and appropriateness of ROOTS for Black and Latiné families (acceptability of intervention measure; intervention appropriateness measure; interview questions on parents' engagement with ROOTS materials)
Implementation process	How implementing the intervention impacts current operating procedures and whose buy‐in, input, and expertise is needed to deliver and sustain the intervention	●	●	Qualitative and quantitative assessments with interventionists about perceived barriers and facilitators to intervention delivery, such as ease of implementation, costs, perception of community buy‐in (e.g., Feasibility of implementation measure)

*Note:* Qual = qualitative measure. Quant = quantitative measure. Some overlap exists between domains in the RE‐AIM and CFIR frameworks. For instance, RE‐AIM's *adoption* and *maintenance* dimensions align with CFIR's *inner setting* and *characteristics of individual* domains, as they reflect organizational readiness and individual perspectives. As a result, several measures correspond to more than one framework domain and are listed in multiple sections of the table to reflect this integration.

**Table 3 jmft70052-tbl-0003:** Main and secondary outcome measures at T1, T2, and T3.

Construct	Measure	Reporter	Description
Main child outcomes			
Social‐emotional functioning	***** *SDQ* (Goodman 1997)	Parent	25 items assessing emotional symptoms, peer problems, conduct problems, hyperactivity, and prosocial behaviors *α* = 0.88 (Palmieri and Smith 2007)
Sleep	Axivity	Objective measure	Average nightly sleep duration and quality over a 7‐day period (Martin and Hakim 2011)
	^ **+** ^ *PCSIS* (Alfano et al. 2013)	Parent	12 items assessing sleep‐related parenting behaviors and interactions, such as sleep dependence, sleep conflict, *α* = 0.82
Physical activity	Axivity	Objective measure	Accelerometer‐derived physical activity intensity (e.g., light, moderate) over a 7‐day period (Lynch et al. 2019)
Sedentary behavior/screen time	Axivity	Objective measure	Accelerometer‐derived sedentary time over a 7‐day period (Lynch et al. 2019)
Secondary parenting outcomes			
Ethnic‐racial socialization attitudes and practices	***** *CSAB* (Derlan et al. 2016)	Parent	17 items assessing attitudes toward ethnic‐racial socialization (12 items) and their use of different ethnic‐racial socialization practices (five items) with their child, *α* = 0.86−0.92
	^+^ *RaSCS* (Anderson et al. 2020)	Parent	Adapted eight items assessing parents' confidence in using various ethnic‐racial socialization strategies
Parenting self‐efficacy	* *****PSAS* (Dumka et al. 1996)	Parent	Five items assessing parents’ confidence in their parenting role, *α* = 0.79 (Matsuda et al. 2019)
Parenting practices	***** *Parenting Scale* (Arnold et al. (1993))	Parent	30 items assessing various dimensions of maladaptive parenting discipline styles, such as laxness (permissive discipline) and over‐reactivity (anger, use of authoritarian discipline), *α* = 0.76−0.84 (López‐Fernández et al. 2022)

*Note:*
^+^Scale has been validated in English. *Scale has been validated in English and Spanish. Abbreviations: Axivity, axivity accelerometer; CSAB, cultural socialization attitudes and behaviors; PCSIS, parent–child sleep interactions scale; PSAS, parenting self‐agency scale; RaSCS, racial socialization competency scale; SDQ, strengths and difficulties questionnaire.

